**Methods:**

This is a crossover trial targeting 40 men and women between 50 and 90 years of age with either mild or moderate symmetric sensorineural hearing loss. Consented, willing participants will be recruited from either an independent living accommodation or via a community database to undergo a 6-month intensive face-to-face auditory training program (active control). Participants will be assigned in random order to receive hearing aid (intervention) for either the first 3 or last 3 months of the 6-month auditory training program. Each participant will be tested at baseline, 3, and 6 months using a neuropsychological battery of computer-based cognitive assessments, together with a depression symptom instrument and a social interaction measure. The primary outcome will be cognitive performance with regard to spatial working memory. Secondary outcome measures include other cognition performance measures, depressive symptoms, social interaction, and hearing satisfaction.

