## Methods

### Trial Design

This study has a randomized crossover trial design. It attained ethics approval on July 22, 2016 (Swinburne’s Human Research Ethics Committee protocol number SHR Project 2016/159).

All participants will undergo an individualized face-to-face auditory training program for a period of 6 months and will be randomly allocated to one of the following groups:

Participants who will be fitted with hearing aids only for the first 3 months of the auditory training program—*Group A.*Participants who will be fitted with hearing aids only for the last 3 months of the auditory training program—*Group B.*

Participants will be tested at baseline, and at 3 and 6 months in terms of cognition, depressive symptoms, social interaction, and hearing satisfaction.

A crossover design is chosen to allow each participant to serve as their own control [39]. Group A participants will have the option to withdraw from the study after 3 months if they decide to purchase hearing aids immediately. Similarly, group B participants will also have the option of withdrawing from the study at any time. As all participants will receive auditory training for the entire duration of the study to address their hearing loss, participants will benefit from the study even when the hearing aid intervention is not in place.

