### Outcome Measures

The primary outcome measure will be changes in cognitive performance as measured by the spatial working memory component of the Swinburne University Computerized Cognitive Assessment Battery (SUCCAB). Reliability and validity assessment has demonstrated that the SUCCAB, especially the spatial working memory component of this battery, is sensitive to aging and intervention and correlates strongly with memory subsets in the Wechsler Adult Intelligence Scale –Fourth Edition [45-47].

Secondary measures include the other SUCCAB cognition measures, social interaction measured using the Berkman-Syme Social Network Index, and depressive symptoms measured using the Geriatric Depression Scale (GDS). Hearing satisfaction (with or without hearing aids) will be measured using the Abbreviated Profile of Hearing Aid Benefit (APHAB) Inventory.

All outcomes will be measured at baseline, after 3 months, and after 6 months (Table 1).

**Table 1 table1:** Schedule of enrollment, interventions, and assessments for study.

Time points		Prescreening telephone call	Baseline assessment T_0_ (<24 days following screening)	Study assessment T_1_ (3-month follow-up)	Study assessment T_2_ (6-month follow-up)

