##### Abbreviated Profile of Hearing Aid Benefit

APHAB [55] is a self-assessment inventory that will be answered by each participant to assess hearing satisfaction (with or without hearing aids). Participants will answer APHAB at baseline, after 3 months, and after 6 months. Four scales of the APHAB will be assessed, namely, (1) ease of communication, (2) effects of background noise, (3) effects of reverberation, such as listening to sounds across a large room, and (4) aversiveness, which will look at uncomfortable loudness of background sounds such as traffic and alarm bells.

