### Statistical Analysis

The following statistical analyses will be performed:

Baseline comparison of the 2 groups in terms of demographics, cognition, depression, social interaction, hearing loss, and hearing satisfaction by reporting descriptive statistics of each group as randomized, and an effect size of the difference using Cohen's d.Comparison of the 2 groups in terms of changes in cognition, depression, and social interaction from baseline to 3 months and 6 months, using a per protocol approach for the crossover analysis [39] and an intention-to-treat, multilevel model analysis [56]. These methods will be used to estimate any carryover effects [57].Analysis of SPT results with and without hearing aids as a measure of the efficacy of hearing aids and auditory training with and without hearing aids using multilevel models and again allowing for carryover effects.Analysis of the speech tracking rates from the two 12-week programs of speech tracking using a learning model as described by Blamey and Alcantara [25]. This analysis will yield learning and forgetting rates with and without hearing aids. These learning and forgetting rates are valid measures of cognitive processes that are likely to be affected by the use of hearing aids. These data will also be analyzed using multilevel models again allowing for carryover effects.Analysis of the aided and unaided scores from APHAB will be used to assess how the benefit of hearing aids differed between groups and over degree of hearing impairment (mild/moderate hearing loss).

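### The stated APHAB contrasts do not test the overall hearing-aid effect: it cancels from the Group A versus Group B comparison, and hearing satisfaction is left out of the crossover analysis item

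*Protocol article*

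**What the plan says.** The protocol article (Methods, Trial Design) describes a two-sequence, two-period crossover: "A crossover design is chosen to allow each participant to serve as their own control". Group A is "Participants who will be fitted with hearing aids only for the first 3 months of the auditory training program" and Group B is "Participants who will be fitted with hearing aids only for the last 3 months of the auditory training program". All participants have weekly auditory training throughout both periods.

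The abstract gives the outcome's status: "Secondary outcome measures include other cognition performance measures, depressive symptoms, social interaction, and hearing satisfaction". Outcome Measures adds: "Hearing satisfaction (with or without hearing aids) will be measured using the Abbreviated Profile of Hearing Aid Benefit (APHAB) Inventory". On timing, the APHAB section says: "Participants will answer APHAB at baseline, after 3 months, and after 6 months".

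In Statistical Analysis, the first item includes hearing satisfaction in a descriptive baseline comparison. The second item, which carries the crossover and multilevel analyses and the carryover estimate, reads "Comparison of the 2 groups in terms of changes in cognition, depression, and social interaction from baseline to 3 months and 6 months". Hearing satisfaction is not in that list. The last item is the only post-baseline APHAB analysis: "Analysis of the aided and unaided scores from APHAB will be used to assess how the benefit of hearing aids differed between groups". The sentence goes on to name a second contrast, benefit by degree of impairment (mild or moderate).

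**The concern.** The trial asks whether aids add something to auditory training. For APHAB that is a comparison of aided with unaided scores, averaged over participants. Both contrasts in the last item instead ask whether the benefit differs between subsets of participants, and one of the subsets is the randomised sequence. A difference in benefit between sequences is the standard route to period and carryover effects, not to the treatment effect.

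Two misreadings could follow. If aids help both groups equally, the group contrast is null, and a reader could take that as no benefit. If aids do nothing but scores move with more training or repeat completion of the inventory, the group contrast can be significant and be reported as a difference in hearing-aid benefit. A period effect is plausible here because Group A's aided score comes after 3 months of training and Group B's after 6.

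**Working it through.** **Plan's own figures.** The document gives no figure for APHAB. Its sample size of 34 (alpha 0.025, 80% power, f = 0.25, two groups, three measures) reproduces as a group-by-time interaction if the within-person correlation is 0.5 and sphericity holds: power at 34 is 0.82, and 34 is the smallest even total reaching 80%. The point below does not affect that number.

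**Notation.** Let tau be the aid effect, p1 and p2 the effects of period and training at 3 and 6 months relative to baseline, and c the carryover into Group A's second period.

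| | Baseline | 3 months | 6 months |
|---|---|---|---|
| Group A | 0 | p1 + tau | p2 + c |
| Group B | 0 | p1 | p2 + tau |

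**What the group contrast estimates.** The article does not settle which unaided score enters the benefit, so there are three readings.

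1. Aided period minus unaided period. A: tau + p1 − p2 − c. B: tau + p2 − p1. A − B = 2(p1 − p2) − c.
2. Aided score minus baseline. A: tau + p1. B: tau + p2. A − B = p1 − p2.
3. Both scores at the same visit. An additive period effect drops out within each person, and A − B is only the difference between the aid effect when aids come first and when they come second.

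A common tau is absent from all three. Under reading 1 the average of the two group benefits, (A + B)/2 = tau − c/2, does recover tau when there is no carryover.

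**The mild/moderate contrast.** This estimates tau(moderate) − tau(mild). An aid effect of equal size in both strata cancels here as well.

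**Size.** Assumptions, none from the document: SD 1 at each visit, within-person correlation 0.5, two-sided 5% test, 20 per group (all 40 analysed).

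- SD of a within-person difference: sqrt(2 × (1 − 0.5)) = 1.
- Standard error of A − B: sqrt(1/20 + 1/20) = 0.316.
- Standard error of the crossover estimate (half the difference in period 1 minus period 2 scores): 0.316/2 = 0.158.

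Rejection rate of the group contrast with tau = 0 and c = 0:

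| Period effect, absolute p1 − p2 | Reading 1, shift / SE | Rejects | Reading 2, shift / SE | Rejects |
|---|---|---|---|---|
| 0.1 SD | 0.2/0.316 = 0.63 | about 9% | 0.1/0.316 = 0.32 | about 6% |
| 0.2 SD | 0.4/0.316 = 1.26 | about 23% | 0.2/0.316 = 0.63 | about 9% |
| 0.3 SD | 0.6/0.316 = 1.90 | about 45% | 0.3/0.316 = 0.95 | about 15% |

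Under reading 3 an additive period effect gives no excess over 5%. With 17 per group, 0.3 SD under reading 1 gives about 40%.

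With a true aid effect and no period or carryover effect (simulation, 17 per group, 20,000 runs, same SD and correlation), the reading 1 group contrast rejects in 4.9% of trials at tau = 0.5 SD and 4.8% at tau = 1 SD. From the same data the crossover estimate averages 0.50 and 1.00 SD, with power of 81% and about 100%. At 20 per group its power for 0.5 SD is about 87%.

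**Carryover.** With tau = 1, p1 = 0.2, p2 = 0.4 and c = 0.3, the crossover estimate averages 0.85, matching tau − c/2 = 1 − 0.15. The group contrast averages −0.70, matching 2(−0.2) − 0.3.

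**The case against.** A reader might infer that the group contrast is the only APHAB analysis and that the outcome has no valid test. The document does not support that. The same sentence names the mild/moderate contrast, and hearing satisfaction is in the baseline comparison. Benefit has to be computed from each participant's aided and unaided scores before it can be compared, so its average is available and testable. Nothing in the sentence excludes that test.

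The group contrast also answers a real question: whether aids help more when fitted at the start of training or after 3 months of it. Rejecting in 5% of trials when the aid effect is large and equal in both groups is correct behaviour for that question, not lost power. The numbered hypotheses cover cognition, depression and social interaction, not hearing satisfaction. The article is condensed, and a missing model specification for a secondary outcome is not in itself a fault. The 45% figure needs an assumed period effect of 0.3 SD and one reading of benefit.

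All of this stands, and it limits the point. It does not remove it. The article does state APHAB contrasts, and neither estimates the overall aid effect. The second item lists its outcomes by name and omits hearing satisfaction, although the item just before it includes it. The speech perception and speech tracking items, equally condensed, name multilevel models with a carryover allowance.

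**Conclusion.** The point holds in a limited form. For APHAB, the two stated post-baseline contrasts are differences in benefit, between sequences and between severity strata. Neither tests whether aided scores differ from unaided scores overall, and the item that would supply that test does not list the outcome. The cancellation of a common aid effect follows from the design alone and needs no numerical assumption.

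The size of the risk of misreading does need assumptions. With SD 1, correlation 0.5, 20 per group and no aid benefit, the false signal runs from about 9% to 45% for period effects of 0.1 to 0.3 SD across periods, from about 6% to 15% against baseline, and stays at 5% if both scores come from one visit. The document gives no period effect, so these are illustrations. The matter concerns one secondary outcome. The primary outcome and the sample size are unaffected. It should be corrected, and because the article reports that analysis is under way, before APHAB results are reported.

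**What to change.** Add hearing satisfaction to the outcomes in the second Statistical Analysis item. Analyse each of the four APHAB scales with the multilevel crossover model already planned there, with terms for aid status, period, carryover or sequence, baseline score and degree of hearing loss. With baseline as a covariate and two follow-up visits, carryover and sequence cannot be separated, so say which one is fitted.

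Report the aid-status coefficient with its confidence interval as the main APHAB result. Use the interaction of aid status with degree of loss for the mild/moderate question. State which unaided score enters the benefit: the other period, baseline, or the same visit. Keep the Group A versus Group B difference in benefit only as a descriptive order/period contrast, labelled as such.

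The cost is a change of analysis wording. The data are the same, with no extra visits or participants.

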### Sample Size

Allowing for 2.5% significance, 80% power, and a moderate effect size (f=0.25), a power analysis indicated that a repeated measures mixed effects design with 3 repeated measures required a total sample size of 34 participants, split evenly between the 2 groups. This allows for the comparison of changes from baseline to 3 and 6 months for the 2 groups. Except for participants from Swinburne’s CHP database who will need to travel to attend their auditory training sessions at Swinburne University, all other participants will attend their appointments at their facilities. As a result, only a 10% allowance was made for attrition resulting in an overall sample size of 40.

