### Assignment of Interventions

#### Allocation

Groups will be matched in terms of the degree of hearing loss (mild or moderate) with 1 member from each matched pair randomly assigned to *Group A* and the other member of each matched pair assigned to *Group B*. Allocation will be performed using a system of envelopes prepared and opened by the researcher at the time of recruitment.

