##### Pure Tone Audiometry in Each Ear

To understand the degree of hearing impairment and classify participants according to the type of hearing loss, hearing ability will be measured at threshold frequencies 0.5, 1, 2, 3, 4 kHz in both ears. The choice of frequency to be tested corresponds to the amplification range of most modern hearing aids and is consistent with capturing sensitivity at frequencies affected by sensorineural hearing loss and noise-induced damage. Only participants with either mild or moderate symmetric sensorineural hearing loss will be included in the study.

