##### Blamey Saunders Speech Perception Test

A Web-based Speech Perception Test (SPT) will be used in addition to the standard audiogram for the purpose of measuring hearing loss. SPT is a monosyllabic word test used to characterize the form and degree of hearing loss [23]. There will be 5 SPT evaluations altogether: SPT will be performed without hearing aids at baseline, after 3 months, and then at 6 months for all participants included in the trial. It will also be performed with hearing aids immediately after participants are fitted with hearing aids for the first time and at the end of 3 months of auditory training while wearing a hearing aid.

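### The APHAB analysis of benefit by degree of hearing loss uses a mild/moderate split although pure-tone thresholds are measured in dB, which weakens a secondary analysis in a small sample

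*Protocol article*

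**What the plan says.** All references are to the protocol article.

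- **Statistical Analysis, last item.** Aided and unaided APHAB scores will be used to assess "how the benefit of hearing aids differed between groups and over degree of hearing impairment (mild/moderate hearing loss". Degree therefore enters this item as a two-level factor.
- **Eligibility Criteria.** Mild is 26-40 dB and moderate is 41-70 dB, for symmetric loss, on a pure-tone average over 0.5 to 4 kHz in both ears. No other definition of the two categories is given.
- **Pure Tone Audiometry in Each Ear.** "hearing ability will be measured at threshold frequencies 0.5, 1, 2, 3, 4 kHz in both ears". A PTA in dB is therefore available before any banding.
- **Allocation.** The same two categories form the matched pairs: "Groups will be matched in terms of the degree of hearing loss (mild or moderate").
- **Outcome Measures.** APHAB (hearing satisfaction) is a secondary measure. The primary measure is spatial working memory.
- **Results.** Recruitment was completed in June 2017 and data analysis was under way at publication.

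**The concern.** The bands were set to decide who may enter the trial. Reused as the degree variable in a model of benefit, they make strong assumptions. A participant at 41 dB is treated as identical to one at 70 dB, while 40 and 41 dB are treated as different. The bands are also unequal, covering 15 and 30 whole-decibel values.

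If benefit changes gradually with hearing loss, a two-level factor captures only part of the relation, and the variation within each band goes into the residual. In a sample of 34 to 40 there is little precision to spare. The practical risk is that a real dependence of aid benefit on degree of loss is missed or poorly estimated, and is then reported as no difference between mild and moderate.

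**Working it through.** **1. The plan's own figure.** The only design calculation in the article is the sample size. Its inputs are "Allowing for 2.5% significance, 80% power, and a moderate effect size (f=0.25"), and the result is that "a repeated measures mixed effects design with 3 repeated measures required a total sample size of 34 participants, split evenly between the 2 groups". For the group-by-time interaction in a repeated-measures ANOVA, the noncentrality is f² × N × m / (1 − ρ), with m = 3 measures. The article does not give ρ, so I assume 0.5. Then λ = 0.0625 × 34 × 3 / 0.5 = 12.75 on 2 and 64 degrees of freedom, and power is 0.821. This makes 34 the smallest even total that reaches 80%. With ρ = 0.3 the total would be 46, and with ρ = 0.7 it would be 22. For attrition, 34 / 0.9 = 37.8, so 38; the stated 40 leaves slightly more room (1 − 34/40 = 15%). None of this depends on the mild/moderate bands. It shows only that the analysis by degree will have about 34 to 40 participants and was not itself a basis for the sample size.

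**2. Information lost by the split.** Information lost = 1 − corr(PTA, band)², with the cut at 40.5 dB. The article gives no PTA distribution, so every row is an assumption.

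| Assumed PTA distribution | Lost |
|---|---|
| Uniform over 26-70 dB: one third mild, 1 − 3 × (1/3) × (2/3) | 33.3% |
| Uniform over 26-55 dB: half mild, 1 − 3 × (1/2) × (1/2) | 25% |
| Normal, split at its median: 1 − 2/π | 36.3% |
| Truncated normal, mean 35-42 dB, SD 6-12 dB (simulated) | 32-47% |
| Truncated normal, mean 45-50 dB, SD 6-12 dB (simulated) | 40-76% |

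The largest losses arise when few participants are mild. The 76% case has mean 50 dB and SD 6 dB, with only 6% of participants in the mild band.

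**3. What that means for power (illustration).** Take a linear relation between PTA and benefit with true correlation r. The split reduces the correlation to r × √(share retained). By the Fisher z approximation, power ≈ Φ(atanh(r) × √(n − 3) − 1.96), two-sided 5%.

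- n = 40, r = 0.4, continuous PTA: atanh(0.4) × √37 = 0.4236 × 6.083 = 2.577. Power is Φ(0.617) = 73%.
- n = 40, r = 0.4, split retaining 65%: the correlation is 0.4 × √0.65 = 0.322, and atanh × √37 = 0.3344 × 6.083 = 2.034. Power is Φ(0.074) = 53%.
- The same at r = 0.5: 92% continuous and 74% with the split.
- n = 34, r = 0.4: 0.4236 × √31 = 2.359, power 65%; with the split, 0.3344 × √31 = 1.862, power 46%.
- Ends of the range at n = 40, r = 0.4: power is 59% if 75% is retained and 23% if 24% is retained.

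Retaining 65% is like analysing 0.65 × 40 = 26 of the 40 participants.

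**The case against.** The strongest case against is that this is a modelling preference about a modifier in a secondary analysis. Analysing by the factor used for matching is conventional and easy to interpret. The article says the scores will be used to assess differences and names no single hypothesis test, so the power figures above are not the power of the planned analysis. They rest on assumed distributions and correlations. Changing the degree variable once analysis has begun would also be a post hoc change. All of this is fair. It limits the size and reach of the point, but it does not remove the loss: every distribution examined loses at least a quarter.

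Several stronger readings are tempting, and the article does not support them.

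- **That the bands are the only measure of degree in the trial.** The Speech Perception Test (SPT) "will be used in addition to the standard audiogram for the purpose of measuring hearing loss", and "SPT is a monosyllabic word test used to characterize the form and degree of hearing loss". It has its own multilevel analysis, in which the bands are not mentioned. Hearing loss also appears in the "Baseline comparison of the 2 groups in terms of demographics, cognition, depression, social interaction, hearing loss, and hearing satisfaction", with no statement that it is reduced to two levels there.
- **That participants with one ear on each side of 40/41 dB have no category, or that a researcher picks the ear.** The article requires symmetric loss and is silent on how such ears are classified. That is operational detail which a condensed article may leave to the full protocol. Nothing in it gives anyone a choice of ear.
- **That the matching rule should change.** Recruitment is complete, so this can no longer be acted on.

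**Conclusion.** The point holds for the APHAB item. That item fixes degree of impairment as two levels although finer data are collected on every participant, and a continuous term is a better use of them. The loss is roughly a third of the PTA information under plausible assumptions. The full range of about 25-76% reflects the lack of any PTA distribution in the article. The fall in power from about 73% to 53% is illustrative: it assumes n = 40, a true linear correlation of 0.4, 65% of the variance retained, and a simple correlation test at two-sided 5%.

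The reach is one secondary analysis. A reader might infer that the primary result or the sample size is affected, but neither is stated to use the bands. The weakness costs precision on how benefit varies with hearing loss; it does not threaten the trial's main comparison.

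**What to change.** In the last item of Statistical Analysis, replace the mild/moderate factor with a continuous five-frequency PTA (0.5, 1, 2, 3 and 4 kHz), together with its interaction with aided condition. Name one summary in advance of the analysis, such as the better-ear or the two-ear average. The article gives no reason to prefer either, and what matters is that one is fixed. Keep mild/moderate for descriptive tables and plots.

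No new data, visits or participants are needed. The statistical cost is a linearity assumption, which a plot of benefit against PTA can check. The procedural cost is timing: data analysis was under way when the article appeared, so the report should say when the continuous term was specified and whether APHAB data had been seen by then.
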